## Abstract

**Background::**

Back pain is one of the most common diseases, and many patients with recurrent pain seek alternative treatment strategies. Thread embedding acupuncture involves thread insertion at the acupuncture point for continuous physical and chemical stimulation. Although thread embedding is widely used in clinical practice, there is no sound evidence of its efficacy for chronic back pain. We describe the protocol for a randomized controlled trial for investigation of the efficacy and safety of thread embedding acupuncture combined with conventional acupuncture for chronic low back pain.

**Methods::**

This randomized, controlled, assessor-blinded, 2-armed, parallel, multicenter clinical trial will include 38 outpatients with chronic low back pain recruited from 4 traditional Korean Medicine hospitals. The patients will be randomly allocated to a treatment group (conventional acupuncture + thread embedding acupuncture) and a control group (only conventional acupuncture) in a 1:1 ratio. The treatment group patients will receive thread embedding acupuncture treatment at 10 acupuncture points (multifidus muscle, 4 points; spinal erector muscles, four points; lumbar quadrate muscle, 2 points) once a week for 8 weeks (8 sessions). In addition, all patients will receive conventional acupuncture treatment at 14 acupuncture points (GV3, EX-B5, and bilateral BL23, BL24, BL25, BL26, BL40, and BL60) twice a week for 8 weeks (16 sessions). The primary outcome will be the change in the visual analog scale score from visit 1 to visit 16, analyzed by independent *t* tests, in both groups. The groups will also be compared with regard to the clinical relevance (minimal clinically important difference), quality of life (3-level version of Euroqol-5D), disability level (Roland and Morris Disability Questionnaire), global assessment (patient global impression of change), and safety. Cost data for cost–benefit and cost-effectiveness analyses will be collected.

**Discussion::**

Our study results will provide evidence of the efficacy and safety of thread embedding acupuncture combined with conventional acupuncture for the management of chronic low back pain. Even though the assessors will be blinded, the patients will not be blinded to treatment because of the lack of a sham embedding acupuncture group; this is a limitation of our study.

**Trial registration::**

Clinical Research Information Service: KCT0002666

## Background

1

In developed countries, more than 70% individuals experience low back pain. Approximately 90% cases of back pain are nonspecific with an unclear pathophysiological origin.^[1,2]^ Back pain is classified as acute, subacute, and chronic according to the pain duration. Conventionally, pain for <6 weeks, 6 to 12 weeks, and >12 weeks is categorized as acute pain, subacute pain, and chronic pain, respectively.^[3]^ Back pain easily recurs without proper treatment and rehabilitation. Psychological factors also prolong back pain.^[4]^ In a cohort of patients with chronic low back pain refractory to general conservative therapy, pain was associated with the facet joint of the spine in 31% cases, sacroiliac joint in 18% cases, and spinal discs in 42% cases.^[5]^ Although conventional western medicine treatment has shown efficacy for the treatment of back pain,^[6]^ several patients still experience pain and require alternative treatment strategies.^[7]^ In fact, the number of patients opting for complementary and alternative medicine (CAM) is gradually increasing.^[8]^ Acupuncture, moxibustion, chiropractic manipulation, massage, yoga, Tai chi, and Qigong are frequently used CAM therapies.^[7,8]^

Thread embedding acupuncture (TEA), a type of dermal needle insertion therapy, involves the insertion of thread at specific points for the treatment of various disorders.^[9]^ Because of sustained stimulation, TEA has been used to treat chronic diseases.^[10]^ TEA provides both physical and chemical stimulation. The former refers to continuous acupuncture point stimulation after thread insertion, while the latter refers to tissue damage caused by thread insertion, which results in an aseptic inflammatory reaction and ultimately promotes tissue regeneration.^[11]^ In the early days, TEA was used to treat obesity for cosmetic purposes. However, it is currently used to treat several musculoskeletal conditions such as ankle sprain,^[12]^ shoulder pain,^[13]^ lumbar intervertebral disc herniation,^[14]^ and plantar fasciitis.^[15]^

In cases of chronic back pain, if the treatment frequency is not maintained for a certain regular period, the success rate decreases and the risk of recurrence increases. TEA stimulates the surrounding spinal muscles and ligaments, while the thread dissolves and promotes the recovery and strengthening of the ligaments and muscles around the waist. Sustained effects of infiltration and the promotion of tissue regeneration enhance the pain-relieving effects. However, most published studies have been case reports, and well-designed randomized controlled clinical trials are necessary to confirm the efficacy and safety of TEA for chronic low back pain. Here, we describe the protocol for a randomized controlled clinical trial for investigation of the efficacy and safety of TEA combined with conventional acupuncture for chronic low back pain via assessments of the pain intensity, disability level, clinical relevance, quality of life, global impression change, and safety outcomes.

## Methods/design

2

This study protocol followed the Standard Protocol Items: Recommendations for Interventional Trials (SPIRIT) checklist, which enhanced the quality of the clinical trial.^[16]^

### Objectives

2.1

The aim of this study was to examine the efficacy and safety of TEA combined with conventional acupuncture for chronic low back pain through comparisons with the effects of conventional acupuncture alone

### Trial design and study setting

2.2

The study is a randomized, sham-controlled, parallel group, assessor-blinded, multicenter, superiority clinical trial. Thirty-eight participants who meet the eligibility criteria will be randomly assigned to a treatment group (TEA + conventional acupuncture) or a control group (only conventional acupuncture) in a 1:1 ratio. The trial design and study flowchart are shown in Fig. 1.

**Figure 1 F1:**
[figure not shown]
Study flowchart.

### Recruitment

2.3

Four Korean Medicine hospitals located in the Republic of Korea, namely Kyung Hee University Korean Medicine Hospital, Kyung Hee University Korean Medicine Hospital at Gangdong, Oriental Medicine Hospital of Daegu Haany University, and Dongguk University Bundang Oriental Hospital, will recruit outpatients in the clinical practice setting. Clinical trial information will be posted on the bulletin board of each hospital and university, in local newspapers, in online advertisements, and on advertisement boards in public spaces.

### Eligibility criteria: inclusion criteria

2.4

1.Male and female subjects aged 19 to 65 years;2.Chief complaint of low back pain for >3 months;3.Pain and discomfort rated beyond 40 mm on a 100-mm visual analog scale (VAS) for 1 week before enrollment;4.Voluntary provision of written informed consent and willingness to follow trial-related instructions.

### Eligibility criteria: exclusion criteria

2.5

1.History of hypersensitive reactions to TEA or conventional acupuncture;2.Abnormal signs in neurological examinations of the lower extremity;3.Previous surgical treatment for severe neurological deficits (motor or sensory) or cauda equine syndrome;4.History of spinal surgery or scheduled spinal surgery during the clinical trial period5.Neuromuscular scoliosis or neurodegenerative disease;6.Diseases that can cause secondary back pain, such as vertebral fracture, inflammatory spondylitis, spinal infection, and malignant tumor;7.Pregnancy, lactation, plans to conceive, or refusal to use appropriate contraception methods during the trial period;8.History of acupuncture, medication, physical therapy, or manipulation therapy for back pain within the last 2 weeks;9.Use of anticoagulants;10.More severe pain in areas other than the lumbar region;11.Ineligibility for the trial judged by the clinical trial investigator.

### Subject withdrawal criteria

2.6

1.Violation of the inclusion criteria or fulfillment of the exclusion criteria;2.Serious adverse events that impede trial continuation;3.Withdrawal of consent by the subject or a legal representative;4.Do not receive 3 consecutive treatment sessions or receipt of <6 TEA sessions;5.Violation of the clinical trial protocol by the investigator or the subject;6.Loss to follow-up;7.Use of medications or treatments that can affect the results of the clinical trial without permission from the investigator;8.Inappropriate progress as judged by the investigator.

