#### Study schedule

2.9.1

The study schedule is presented in Table 1. The trial will include a screening phase, treatment phase, and follow-up phase. At the screening visit, participants will sign the informed consent form. The investigator will perform a physical examination, record the medical history, obtain an L-spine X-ray, collect blood samples, record any concomitant treatment history, and use VAS to determine whether the participant is eligible for the clinical trial. If the participant is taking anti-inflammatory drugs or pain killers, we will implement a 2-week washout period. During the 8 weeks of treatment, the patient will visit the facility twice a week (16 visits). Conventional acupuncture treatment will be administered at every visit in both the treatment group and the control group. Eight sessions of TEA will be conducted once a week only in the treatment group (visits 1, 3, 5, 7, 9, 11, 13, 15). On visits 17, the participants will visit the facility 12 weeks after visit 16. VAS scores for pain will be determined on visits 1, 4 (week 2), 8 (week 4), 12 (week 6), 16 (week 8), and 17 (week 20).

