### Outcome measures: primary endpoint

2.10

The primary outcome of our study will be the change in the VAS score for pain from baseline (visit 1) to treatment completion (week 8, visit 16).^[18]^ The patient will quantify the pain intensity by marking the most relevant point on a 100-mm horizontal line anchored by 2 descriptors: 100, representing the “worst imaginable pain,” and 0, representing “no pain.”

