### Sample size calculation

2.14

Sample size calculation was performed to determine the appropriate number of participants. The primary outcome will be the change in the VAS score from visit 1 to visit 16 in the treatment and control groups. To our knowledge, no study has investigated the effects of TEA combined with conventional acupuncture treatment. A previous clinical trial evaluated the effects of TEA and sham TEA administered for 4 weeks.^[24]^ The change in the VAS score after treatment (week 4) was 1.85 ± 0.86 in the treatment group and 0.5 ± 0.80 in the control group. The required number of participants per group was 11, considering a 2-tailed test with a 1:1 allocation ratio, a superiority trial, a test power of 95% (1-β), and a significance level of 5% (α). After considering a 40% dropout rate, we calculated the sample size for our study to be 19 patients per group. Thus, a total of 38 participants will be required.

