### Statistical analysis

2.15

Data will be expressed as means and standard deviations for continuous variables and frequencies and ratios (%) for categorical variables. The patients’ baseline characteristics will be compared using an independent *t* test or the Wilcoxon rank-sum test for continuous variables and a χ^2^ test or Fisher exact test for categorical variables. If there is a significant difference in the baseline characteristics between groups, analysis of covariance will be used for efficacy analysis, which will include both a full analysis set (FAS) and a per-protocol set (PPS). FAS will be used for the main analysis and PPS will be used for subanalysis of sensitivity. FAS will include patients who will receive at least 1 session of treatment and will undergo at least 1 pain assessment using VAS after treatment. FAS will not include participants who do not meet the eligibility criteria, those who do not receive any treatment, or those whose data are not acquired after randomization. PPS will include patients who will receive at least 12 sessions of treatment (75% compliance rate), those who undergo pain assessment using VAS at visit 16, and those who will complete the clinical trial without major protocol violation. In the primary outcome analysis, the change in the VAS score from visit 1 to visit 16 will be compared between the treatment group and the control group using an independent *t* test or the Wilcoxon rank-sum test according to normality. In the secondary outcome analysis of continuous variables, a *t* test or the Wilcoxon rank-sum test will be applied according to normality. In the secondary outcome analysis of categorical variables, a χ^2^ test or Fisher exact test will be applied. In safety analysis, the total adverse event ratio and adverse event ratio associated with TEA will be compared using a χ^2^ test or Fisher exact test. The last observation carried forward method will be used for missing data. The level of significance will be 5% (2-tailed test). No correction method will be applied for multiple comparisons in the secondary outcome analysis.

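### Withdrawal criterion 5 (section 2.6) covers protocol violations by patient or investigator without a severity limit, so week 8 VAS values may be lost unnecessarily

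*Protocol article*

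**What the plan says.** Section 2.6 of the protocol article lists eight withdrawal criteria. Item 5 reads in full "Violation of the clinical trial protocol by the investigator or the subject". It has no qualifier such as major or serious, and it expressly reaches violations by the investigator. Other parts of the article do set limits. Item 2 covers only serious adverse events that prevent the patient from continuing, item 4 sets numerical thresholds for missed treatment, and section 2.15 keeps in the per-protocol set (PPS) only "those who will complete the clinical trial without major protocol violation", among other conditions.

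The primary endpoint (section 2.10) is the change in VAS from visit 1 to visit 16, at week 8. After baseline, VAS is scheduled at visits 4, 8, 12, 16 and 17 (section 2.9.1). The main analysis uses the FAS, which requires at least one treatment session and that the patient "will undergo at least 1 pain assessment using VAS after treatment". For gaps, section 2.15 states: "The last observation carried forward method will be used for missing data". The article describes no assessments after withdrawal.

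**The concern.** A withdrawal criterion decides whether a randomised patient can still supply the primary outcome. Item 5 puts no lower bound on the departure that may count, and it allows a patient to be withdrawn for someone else's error. Many departures of that kind do not make further assessment unsafe or uninformative.

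What is at stake is the week 8 VAS. If measurement stops when the patient is withdrawn, the main analysis either loses the patient or uses a value recorded part-way through treatment. Neither is needed to handle violations in the analysis, because the PPS rule already sets major violators aside. Participants and practitioners are unblinded (section 2.8), so it matters that the plan not allow more loss of outcome data than it must.

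**Working it through.** **The plan's own figure.** Section 2.14 gives mean changes of 1.85 (SD 0.86) and 0.5 (SD 0.80), two-sided 5% alpha and 95% power.

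- Pooled SD = √((0.86² + 0.80²)/2) = 0.8305.
- Standardised difference = (1.85 − 0.5)/0.8305 = 1.625.
- By the noncentral t distribution, 10 per group gives power 0.930 and 11 per group gives 0.952, so 11 per group is reproduced.
- With 40% dropout, 11/(1 − 0.40) = 18.3, rounded up to 19 per group and 38 in total. This agrees with the plan.
- The allowance covers a loss of 19 − 11 = 8 patients per arm.

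**How far item 5 reaches.** Ineligibility is covered by item 1, missed sessions by item 4 and unpermitted treatment by item 7. If every deviation were meant to trigger withdrawal, the thresholds in item 4 would serve no purpose. The PPS condition also presupposes that patients with lesser violations can complete the trial. Item 5 is therefore best read as covering what the other items leave over. Within that remainder its wording draws no line.

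**What happens to one withdrawn patient.** Inputs are the VAS visits 4 (week 2), 8 (week 4), 12 (week 6) and 16 (week 8), and the thread embedding acupuncture (TEA) visits 1, 3, 5, 7, 9, 11, 13 and 15, all from section 2.9.1. On the latter the article says: "Eight sessions of TEA will be conducted once a week only in the treatment group". Assumption: a VAS due at the withdrawal visit is taken first, and none is taken afterwards. Gap = 8 − week of the last VAS.

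| Withdrawn at visits | Last post-treatment VAS | Weeks carried to week 8 | TEA sessions before that VAS (treatment arm) | Main analysis |
|---|---|---|---|---|
| 1–3 | none | – | – | out of the FAS |
| 4–7 | week 2 | 8 − 2 = 6 | visits 1, 3: 2 of 8 | in the FAS by LOCF |
| 8–11 | week 4 | 8 − 4 = 4 | visits 1, 3, 5, 7: 4 of 8 | in the FAS by LOCF |
| 12–15 | week 6 | 8 − 6 = 2 | visits 1, 3, 5, 7, 9, 11: 6 of 8 | in the FAS by LOCF |

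One patient is 1/19 = 5.3% of an arm and 1/38 = 2.6% of the sample. Under the same assumption a patient withdrawn for a minor violation also leaves the PPS, because that set requires the visit 16 VAS and completion of the trial.

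**What cannot be computed.** The article gives no violation rate, overall or by arm. The number of patients affected, and the direction and size of any bias, are therefore unknown.

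**The case against.** The strongest reply is that item 5 is only a ground for withdrawal in a list, that its neighbours show it to be residual, and that nothing makes withdrawal automatic. This stands. A reader might infer that any deviation, however slight, removes a patient. Item 4 and the PPS condition speak against that. A reader might also infer a contradiction between sections 2.6 and 2.15. There is none, since one governs participation and the other the analysis sets.

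A second reply is that a journal article condenses the full protocol, which may grade violations and provide for assessments after withdrawal. In part this stands: the article does not say outright that VAS collection stops. Still, item 5 sits in one list with withdrawn consent and loss to follow-up, and no later follow-up is described, so stopping is the natural reading. The objection is to the criterion as printed, not to a detail left out.

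Third, the carry-forward consequence applies to every early exit, not only to item 5. That is true. The difference is that exits under item 5 can be avoided: a protocol departure need not prevent a patient from marking a VAS line at week 8.

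Fourth, the sample size already allows for losses: "After considering a 40% dropout rate, we calculated the sample size for our study to be 19 patients per group". This answers a concern about power, and power is not the concern. The allowance protects numbers but does not supply a week 8 value for a patient whose earlier VAS is carried forward.

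Finally, a reader might infer that item 5 biases the comparison, since practitioners are unblinded and only the treatment arm has TEA sessions that could be performed wrongly. Withdrawal that differs by arm is possible on this design, but the documents contain nothing to show that it occurs or which way it would act.

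**Conclusion.** The point holds in limited form. Item 5 has no severity limit and, as worded, permits a randomised patient to be withdrawn for departures, including investigator errors, that need not end participation. It is probably a residual clause and not an automatic trigger.

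The consequence for each patient depends on VAS collection ending at withdrawal, which is implied but not stated. On that assumption the patient is either lost from the FAS or represented at week 8 by a value 2, 4 or 6 weeks old. If VAS collection in fact continues, both effects disappear. No bias, and no shortfall in power, has been shown. The change is worth making because the loss is avoidable and the PPS rule already deals with major violators. Confidence is medium.

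**What to change.** Reword item 5 so that it covers major violations only, and so that these stop study treatment without ending participation. Unless the patient withdraws consent, continue VAS at the visits already scheduled, through 16 and 17. Use those observed values in the FAS in place of LOCF, keeping the existing FAS exclusion for ineligible patients. Let a major violation exclude from the PPS only.

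The cost is small: one reworded item with a sentence each on follow-up and analysis, made as a protocol revision. It needs no extra patients and no new visits. The downside is a little more follow-up of patients who are off treatment, at visits already planned. Their week 8 values will reflect the assigned strategy and not a full course of treatment, while the PPS remains available as the sensitivity analysis. Item 8, which leaves withdrawal for unsuitable progress to the investigator's judgement, is not closed by this change.

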### Randomization and allocation concealment

2.7

A randomization table for each hospital will be created by an independent statistician using the block randomization method with SAS Version 9.4 (SAS institute. Inc., Cary, NC). The randomization number will be sealed in a sequentially numbered opaque envelope and sent to each hospital. The random number envelope will be kept in a double locked cabinet. Consent will be obtained by a Korean Medicine doctor. If the participant voluntarily signs informed consent and meets the inclusion criteria, the clinical research coordinator (CRC) will sequentially give the sealed random number envelope to the physician, who will open the envelope and allocate the participant to the treatment or control group according to the random number.

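### Randomisation is stratified by hospital but the planned tests ignore hospital; if VAS change differs between hospitals the analysis is conservative, though the sample size still stands.

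*Protocol article*

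**What the plan says.** Under Recruitment, the protocol article names the sites: "Four Korean Medicine hospitals located in the Republic of Korea". Under Randomization and allocation concealment it states: "A randomization table for each hospital will be created by an independent statistician using the block randomization method". Separate blocked lists per hospital are randomisation stratified by hospital. The block size is not given.

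Under Statistical analysis, the primary outcome (VAS change over the treatment period) "will be compared between the treatment group and the control group using an independent *t* test or the Wilcoxon rank-sum test according to normality". The Abstract also names independent t tests for this outcome. Continuous secondary outcomes get the same pair of tests; categorical secondary outcomes and adverse event ratios get a χ² or Fisher exact test. Hospital appears in none of these.

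The only route to covariate adjustment is conditional: "If there is a significant difference in the baseline characteristics between groups, analysis of covariance will be used for efficacy analysis". Hospital is not named there either.

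**The concern.** Blocking within hospital puts nearly equal numbers of each arm in every hospital. A shift in outcome common to all patients of one hospital then cancels from the treatment difference, so the true variance of that difference excludes between-hospital variation. A two-sample t test still counts that variation in its residual. Where hospitals differ, its standard error is too large, its confidence interval too wide and its type I error below the stated 5%. The same mismatch affects the rank-sum and categorical tests.

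The conditional ANCOVA would not repair this. It is triggered by a significant baseline difference between arms, and the blocked lists keep hospital balanced between arms, so the trigger would hardly ever bring hospital in.

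At stake is precision in a trial of 38 patients, not the credibility of a positive result.

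**Working it through.** **Inputs from the protocol article.** Four hospitals; 1:1 allocation; VAS change "was 1.85 ± 0.86 in the treatment group and 0.5 ± 0.80 in the control group"; 95% power and two-sided 5% significance; "The required number of participants per group was 11"; 40% dropout; 19 per group, 38 in total.

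**Assumed, because the protocol does not give them.** ICC (the share of the variance of VAS change that lies between hospitals), taken from 0 to 0.30; hospital sizes 10/10/10/8 for 38 patients and 6/6/6/4 for 22; exact 1:1 balance within hospital; total SD held fixed.

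**Step 1: the protocol's own sample size.** Pooled SD = √((0.86² + 0.80²)/2) = √0.6898 = 0.8305. Difference = 1.85 − 0.5 = 1.35. Standardised effect = 1.35/0.8305 = 1.625. The noncentral t distribution gives power 0.930 at 10 per group and 0.952 at 11, so 11 reproduces. Then 11/0.6 = 18.3, rounded up to 19 per group. The stated figures are correct for an unadjusted t test.

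**Step 2: standard error at ICC ρ = 0.20, n = 19 per arm.**
- True standard error: SD × √(2(1 − ρ)/n) = 0.8305 × √(1.6/19) = 0.241.
- Share of between-hospital variance that stays in the within-arm variance, with 5, 5, 5 and 4 patients per arm: (19 − 91/19)/18 = 0.789, where 91 = 25 + 25 + 25 + 16.
- Root of the expected estimated variance: 0.8305 × √(2(0.8 + 0.789 × 0.2)/19) = 0.264. The simulated mean of the estimated standard error is slightly lower, 0.261.
- Ratio: 0.261/0.241 = 1.08, about 8% too large. The model with hospital gives 0.239.

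**Step 3: simulation, 38 patients, 40,000 trials per setting** (t test v linear model with hospital as a fixed factor).

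| ICC | Type I error, t test v adjusted | Mean 95% CI half-width | Power at a difference of 0.65 (assumed) |
|---|---|---|---|
| 0 | 5.1% v 5.1% | 0.543 v 0.544 | 65.1% v 64.9% |
| 0.05 | 4.7% v 5.1% | 0.540 v 0.531 | 66.2% v 67.6% |
| 0.10 | 4.2% v 5.0% | 0.537 v 0.516 | 66.5% v 69.2% |
| 0.20 | 3.5% v 4.9% | 0.530 v 0.487 | 68.7% v 74.8% |
| 0.30 | 2.8% v 5.0% | 0.524 v 0.455 | 70.1% v 79.7% |

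Further runs gave 3.4% at ICC 0.20 and 3.0% at ICC 0.30 for the t test. With blocks of 4 (assumed), which can leave hospitals slightly unbalanced, type I error was 4.0%, 3.7% and 3.2% at ICC 0.10, 0.20 and 0.30.

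The difference of 0.65 is a standardised effect of 0.65/0.8305 = 0.78. The power forgone is 69.2 − 66.5 = 2.7, 74.8 − 68.7 = 6.1 and 79.7 − 70.1 = 9.6 points at ICC 0.10, 0.20 and 0.30. At a standardised effect of 0.675, with blocks of 4, power was 53% v 56%, 55% v 62% and 56% v 67%: 3, 7 and 11 points.

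**Step 4: power at the planned difference of 1.35 with 22 patients** (the 11 per group left after the allowed dropout). 96.0% v 96.6% at ICC 0.10, 96.9% v 97.9% at 0.20, 97.6% v 98.9% at 0.30. The forgone power is about 1.4 points at most. With 38 patients both analyses have at least 99.8% power, to rounding.

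**Step 5: cost of adjusting when hospitals do not differ (ICC 0).** With 22 patients, power is 95.4% v 95.0% at a difference of 1.35 and 41.2% v 40.6% at 0.65. The cost is about half a point, and 1 point at most over all the settings tried.

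**The case against.** The strongest reply concerns consequence. Nothing in the protocol shows that hospitals differ in VAS change. The outcome is a change from visit 1, so constant hospital differences in pain level cancel, and eligibility, points and schedule are common to all sites. At ICC 0.05 the effect is negligible. This stands, and it makes the finding conditional.

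Three stronger readings are tempting, and the document supports none of them.

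- *That the trial loses power it relied on.* With total SD fixed, the t test's power does not fall as the ICC rises; the last column of the table shows a slight rise. What is forgone is an available gain. A large loss appears only if the true effect is well below the planning effect. That is plausible, since the article's Discussion says the source trial compared TEA with sham TEA over 4 weeks, but it is a separate question about the sample size.
- *That differences between the practitioners giving TEA make adjustment necessary.* TEA is given in one arm only, so such differences are a treatment-by-hospital interaction, not a shift common to both arms. With hospital effects in the TEA arm only (38 patients, standardised effect 0.675), adding hospital moved power from 54.8% to 55.0%, 56.8% to 57.7% and 59.8% to 61.4% at variance shares of 0.10, 0.20 and 0.30. Only differences common to both arms, such as patient mix, give the gains above.
- *That results could be falsely positive.* The error runs the other way.

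It could also be said that a statistical analysis plan may supply the hospital term. But the protocol names the tests, and neither a two-sample t test nor a rank-sum test has room for hospital. A plan that adjusted would depart from the stated primary analysis.

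**Conclusion.** The mismatch between design and analysis is real and stands in the protocol's own text. Its direction is certain where outcomes differ between hospitals: the unadjusted test is conservative and its intervals are too wide. Its size is not known, because it depends on an ICC that the protocol does not give. Over an assumed range of 0.05 to 0.30 with 38 patients, type I error is about 4.7% down to about 3%; at zero there is no loss.

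The sample size of 19 per group reproduces and is not undermined. The power forgone matters only if the standardised effect is less than half the planned 1.6: about 3 to 10 points at 0.78, and 3 to 11 at 0.68, for ICC 0.10 to 0.30. This is an efficiency point of minor to moderate weight. It is worth acting on because the change costs almost nothing if hospitals turn out alike.

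**What to change.** State in the Statistical analysis section that:

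- the primary and continuous secondary outcomes are analysed by a linear model with treatment and hospital (fixed effect);
- if normality fails, a hospital-stratified rank-sum test (van Elteren) replaces the Wilcoxon rank-sum test;
- the responder proportions (MCID, 30% and 50% decreases) are compared by a Cochran-Mantel-Haenszel or exact stratified test;
- hospitals with very few patients are pooled by a rule fixed before unblinding. Four hospitals share 38 patients with 40% dropout allowed, so strata can become sparse.

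The cost is a few lines of text and 3 degrees of freedom (33 instead of 36 with 38 patients), worth about 0.5 to 1 point of power if hospitals do not differ. Patients, visits and sample size are unchanged.
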